### Intervention

The CHAMPION intervention incorporates mHealth technology to emphasize informed, shared decision-making for patients, decision partners and healthcare providers through values clarification, involvement preference, and HRQOL feedback [34, 35]. This decision aid is a comprehensive, cognitive-behavioral skills program that utilizes seven key components suggested by the theoretical framework to assist patients and their decision partners with goal-setting, establishing desired decision control, and facilitating discussions between oncology providers. The seven key decision aid components (see Table 2) are applied during any of three single-event decisions during the advanced cancer trajectory: (1) starting, (2) changing, or (3) stopping anti-cancer treatment [40].

**Table 2 Tab2:** Description of seven key decision aid components [41]

1. **Anticipatory guidance** for managing treatment side effects, quality-of-life and available therapies delivered via pamphlets from National Cancer Institute, Cancer Care National Office, or institutionally distributed.	
2. **Social support** provided by the decision partner’s participation in the study and interactions with the CPN.	
3. **Patient’s preferences for treatment decision-making participation** is assessed and shared with health care providers.	
4. **Decision-making process tutorial** communicates the importance of decision-making and satisfaction via an easy-recall teaching method that addresses (a) the purpose of the decision aid, (b) possible outcomes, (c) preconditions, (d) theory utility, (e) styles of decision making, (f) the steps/process of decision making, and (g) evaluation criteria. This is presented in a 12-min, easy-to-follow audio file and a follow-along transcript.	
5. **Normalization/experiential** context using the *“*Cancer Survival Toolbox: An Audio Resource Program*”* In this National Cancer Institute golden star award program, patients with specific cancer concerns demonstrate practical treatment tools for daily life.	
6. **Values clarification throughout the treatment decisions** through the use of a balance sheet, a simple table identifying the pros and cons for self and others (family and friends), resulting in values clarification for the patient-decision partner dyad. The balance sheet will be used during interactions within patient-decision partner dyads and with the CPN and oncology providers.	
7. **Structured time/data sharing** (i.e., balance sheet and HRQL-PSY graphical summaries) **with oncology providers** to support the oncology provider’s interactions with the patient-decision partner dyad and facilitate decisions.	

The decision-making tutorial is initially presented with a practice decision balance sheet (“telling others about cancer”) as the first decision and, in brief, as a “booster” for subsequent decisions [40]. The practice decision is meant to be less consequential and threatening than the three single-event decisions, allowing participants to practice decision skills. Once patients receive initial treatment options from their providers, they undertake values clarification using the balance sheets with the CPN before the next clinic visit. Structured time with the CPN and enhanced communication with oncology providers related to the decision process is an important intervention component, promoting multidisciplinary collaboration to address issues related to disease progression. Through this interactive process, the mHealth decision aid emphasizes informed, shared decision-making for patients, decision partners, the CPN, and oncologist through values clarification and decision preference. Reports of intervention adherence are collected from participants and the research team. The mHealth decision aid delivery approach allows patients to make informed, quality decisions by cancer care educational audio files, by immediate and over time HRQL-PSY graphical summaries, and by decision balance sheets, while including a support structure with the decision partner, CPN, and oncologist.

A participant has the option to withdraw from the study if they no longer wish to participate in the study, or if a patient dies during the study that is not related to the protocol, then he will be withdrawn from the study. Standard of care is allowed as part of the intervention, which includes pamphlets and brochures of the anti-cancer treatment that is provided by the healthcare provider, but oral, written, or recorded materials related to decision making are not permitted. There will be no blinding to group assignments with the exception of the data analysts. We learned from pilot studies that having CPNs dedicated to either the decision intervention group or enhanced usual care group alleviates treatment diffusion issues.

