## Methods/design

### Study design, setting, and population

The CHAMPION study is an ongoing randomized control trial to assess the effectiveness of a decision intervention (DI) compared to enhanced usual care (EUC) alone. Participants enter the study at one of three single-event decisions: (1) starting, (2) changing, or (3) stopping anti-cancer treatment. For example, a patient being monitored after primary cancer treatment who is diagnosed with disease progression and offered new treatment options would be eligible for this study. Alternatively, a patient who does not respond to, or experiences side effects from, their first choice of treatment and is now considering changing to a new treatment would also be eligible. An example of stopping treatment is a patient who has been on Androgen Deprivation Therapy and is considering stopping treatment. The unit of randomization is the patient-decision partner dyad, with stratification based upon the patient’s race (African American, White, or Other), and by decision event (starting, changing, or stopping anti-cancer treatment). Dyads will be randomly assigned after baseline data collection using a computerized random number generator weighted to have a greater number of DI than EUC dyads. Dyads will be randomized by a study team member, who will have access to sealed envelopes in the event that the computer system is not operational.

A pre-test/post-test design (see Fig. 1) for the three single-event decisions (starting, changing, or stopping anti-cancer treatment) is employed to assess change in HRQL-PSY, decisional conflict, and decision regret. Qualitative methods (post-intervention interviews) are combined with quantitative measurement to enhance the understanding of the patient-decision partner dyads’ experiences using the mHealth decision aid, particularly, in regard to their race and decision event. Patients and decision partners are randomly assigned as a dyad to one of two study arms: EUC or DI. EUC participants receive CPN-administered standard-of-care cancer educational materials not specific to decision making. DI participants receive CPN-administered standard-of-care cancer educational materials plus a previously piloted multicomponent intervention that is designed to facilitate decision partner involvement in the decision-making and communication within the patient-decision partner dyad, as well as between the dyad and the oncologist. Figure 2 displays the CHAMPION study design flow chart.

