**Fig. 2 Fig2:**
[figure not shown]
CHAMPION study design flow chart

The study setting includes three National Cancer Institute designated academic medical centers in the mid-Atlantic region of the USA: the University of Virginia (UVa), Johns Hopkins University (JHU), and Virginia Commonwealth University (VCU). The UVa Cancer Center predominantly serves rural areas in South, Southwest, Central, and North-Central Virginia [41] with approximately 11% of the catchment area residents being African American and 4% Hispanic. The Sydney Kimmel Comprehensive Cancer Center at JHU draws patients from Baltimore City and the surrounding area, as well as those seeking clinical trials, with approximately 20% of the patients being African American and 3% Hispanic. The VCU Massey Cancer Center predominantly serves rural areas in Central-East and Central-West Virginia [42, 43], with approximately 27% of the catchment area residents being African American and 6% Hispanic.

Patient inclusion criteria include the following: a diagnosis of stage III/IV prostate cancer, life expectancy of ≥ 6 months, Karnofsky Performance Status [44] ≥ 60, age ≥ 18 years, and the ability to understand English. Exclusion criteria include the following: severe psychiatric problem, prior non-prostate malignancy in the past 3 years (except treated basal cell/squamous cell skin cancer or superficial bladder cancer), and cognitive impairment. A s*evere psychiatric problem* is defined as inpatient psychiatric treatment in the past 6 months, current treatment with antipsychotic medication, current hallucinations, and/or current serious thoughts of suicide. Cognitive impairment is defined as an adjusted error score of > 5 on the Short Portable Mental Status Questionnaire or other issues preventing participation. A decision partner is defined in the eligibility criteria as a person that the patient identifies as supporting the patient in the decision-making. Consistent with the literature definitions [7], the decision partner is most often a spouse, but can also be an adult family member, friend, or spiritual advisor. In the present study, participants were asked to identify a single decision partner. For illustrative purposes, a ‘typical’ patient-decision partner dyad in this study appears as described in Table 1.

**Table 1 Tab1:** A “typical” CHAMPION study dyad (composite case)

	Age	Race	Ethnicity	Insurance	Employment
Patient	67	African American	Non-Hispanic	Public and private	Employed

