### Recruitment

Recruitment began in 2017 at UVa and JHU, and in 2019 at VCU. Participants are screened at each site using a variety of methods, including research team attendance at weekly clinical case discussions, manual chart review, and referrals from the clinical team. In this event-driven design, oncology clinic providers identify relevant events, such as the patient’s need to address starting, changing, or stopping treatment, and then refer eligible patient-decision partner dyads during weekly clinical trials meetings by teleconferences held at all institutions. In addition, the research teams attend weekly case discussions and discuss patients who may meet the eligibility criteria. The research team subsequently reviews these patients’ medical charts to determine eligibility. If a patient is eligible, the research team addresses the opportunity to participate in the study at the patient’s next clinical visit or over the telephone.

After confirming eligibility, the oncologist or another care provider introduces the study to the patient and decision partner. Patients experiencing serologic, radiographic, or symptom progression are contacted by the research team. The majority of patients and/or dyads are approached directly before or after their clinical visit with the medical oncologist. The research team reviews the study and, if the patient and/or the patient-decision partner dyad is willing, engages in an informed consent process to obtain oral consent or a signature from the patient and the decision partner, as approved by the facilities’ institutional review board (IRB). No data is planned to be used for further studies, which would constitute obtaining additional consent from current participants.

A previous version of the protocol required a decision partner for participation, but this requirement was removed after the study began, based on expert advice and research team discussion regarding the additional value of including patients without decision partners in the study. In the decision to include patients without decisional partners, there is a potential limitation in the analyses to compare between those patients who have decisional partners with those without decisional partners. We will plan to examine differences between dyads and single participants, particularly related to decisional conflict, regret, and quality of life.

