### Data collection and study measures

Data collection is implemented in a secure database system designed at the UVa and is accessible only to limited internet-provided addresses. All data are kept on an encrypted server and participants are given a unique identifier. The minimum necessary number of research team members is given access to the data to help protect participant confidentiality. The measures are collected using mobile devices, allowing the research team to be flexible about where the data are collected and to adapt to patient and decision partner preferences regarding data collection. The research team monitors for participant and decision partner distress signs (e.g., fatigue, anxiety) and, to monitor participant burden on an ongoing basis, probes for feedback about participant reactions. Although depression and other signs of psychological stress are not considered an adverse event, if a patient or decision partner is determined to be at risk for depression—defined as a score of 16 or greater on the Center for Epidemiologic Studies Depression Scale [45]—they are referred to a mental health specialist. A member of the research team meets with each dyad (EUC and DI) for approximately 1 h at baseline and 20 min at each 3-month visit over the 9 months during which participants are enrolled in the study. All participants receive regular in-person or telephone contact by the CPN. This serves the purpose of helping participants access needed resources and keeps them engaged in the study to help retention. The mHealth delivery approach allows patients to make informed, quality decisions via decisional balance sheets, an audio cancer decision-making tutorial, and HRQL-PSY graphical summaries.

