### Statistical analysis and power calculation

The main goal of this mixed-methods research is to test whether the decision support intervention is performing as hypothesized and warrants further research; thus, one-sided testing will be employed. The analysis plan assumes accrual (*N* = 158 dyads) for the quantitative portion of the study and a 15% dropout rate and assumes that the research team will have complete data on 134 dyads, providing approximately 89% power to detect an effect size of 0.5 for change in the main outcome measures for the DI group compared to no change in the EUC group using case-wise deletion. These calculations are informed by pilot data. Considering not all participants will be a dyad, and a smaller number will be single participants, it is unlikely that this would affect the power of the study. This will be reported in future dissemination materials once the study is completed.

For quantitative measures, descriptive analyses will be conducted as appropriate. Change in primary outcomes before and after the intervention will be assessed with analysis of covariance models that include the stratification factors (race and decision event), time, intervention arm, and a time-by-intervention-arm interaction. Additional analyses will assess whether the magnitude of change in primary outcome variables is similar between each member of the dyad using regression models that account for the correlation between each dyad and within participants over time. *Intention-to-treat* is defined as the analysis of all eligible patient-decision partner dyads by treatment as randomized, regardless of compliance with the intervention. Depending on the extent to which the data contain missing data, imputation will be considered for both the dyads and individual participants. Two methods will be used: (1) primary results will be based on an intention-to-treat analysis so that all eligible patients who entered the study will be included in the analyses regardless of compliance and (2) analyses will also include analysis of evaluable cases with more than 80% compliance (operationalized as completed all visits, all parts of the intervention but the home module, and had no other protocol violations) [48]. Using intention-to-treat analysis takes into consideration the bias of dropouts, but using both analyses provide more confidence in the conclusions of the trial if both analyses produce similar effects [48].

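### Navigators appear to be nested within arm, yet the primary model and the 89% power treat dyads as independent

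*Protocol article*

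**What the plan says.** CPNs work in both arms. Under Study design, setting, and population, "EUC participants receive CPN-administered standard-of-care cancer educational materials not specific to decision making"; the decision intervention (DI) arm receives these materials plus the multicomponent intervention. Under Data collection and study measures, "All participants receive regular in-person or telephone contact by the CPN". The Intervention section adds, as a lesson from pilot studies, that "having CPNs dedicated to either the decision intervention group or enhanced usual care group alleviates treatment diffusion issues".

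On randomization, "The unit of randomization is the patient-decision partner dyad", stratified by the patient's race and by decision event. The setting is "three National Cancer Institute designated academic medical centers", and "Recruitment began in 2017 at UVa and JHU, and in 2019 at VCU". Site is not a stratification factor.

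Under Statistical analysis and power calculation, the primary analysis of covariance models "include the stratification factors (race and decision event), time, intervention arm, and a time-by-intervention-arm interaction". The additional analyses allow for correlation within dyads and within participants over time. Power is about 89% for an effect size of 0.5 with 134 complete dyads and one-sided testing. Neither the model nor the power statement mentions navigator or site.

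**The concern.** In the DI arm the CPN is part of the treatment: CPN contact is listed as a source of social support, and the values-clarification exercise is done with the CPN. Dyads who share a CPN may therefore have more similar decisional conflict, regret and quality-of-life scores than dyads who do not. If each CPN serves one arm only, differences between individual CPNs do not cancel between arms. They become part of the arm contrast, and randomizing dyads does not remove them.

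A model that ignores this credits the arm effect with the precision of 134 independent units, when part of the variation comes from a handful of CPNs. The trial uses one-sided testing to decide whether the intervention merits further research, so an inflated false-positive rate bears directly on that decision. The planned power would also be lower than readers are told.

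**Working it through.** **Inputs from the protocol:** 158 dyads, 15% dropout, 134 complete dyads, effect size 0.5, one-sided test, three sites, CPN contact in both arms.

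**Assumed, because not given:** one-sided alpha 0.05; 1:1 allocation (the protocol says only that allocation favours DI); *k* CPNs per arm with equal caseloads; the ICC, ρ, equal in both arms unless stated otherwise.

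**Step 1: the stated power.** 158 × 0.85 = 134.3, so 67 dyads per arm. The noncentrality is 0.5 / √(2/67) = 2.894. Power is Φ(2.894 − 1.645) = 89.4%, or 89.1% with the noncentral t on 132 df. This matches the stated figure, with no allowance for clustering. Allocation of 1.5:1 gives 88.3% and 2:1 gives 86.1%. At one-sided 0.025 with 1:1 it is 82.5%, which does not match.

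**Step 2: CPN as a random effect nested in arm.** In SD units, Var(arm difference) = 2ρ/k + (1 − ρ)(2/67). Divided by 2/67, this is the design effect DE = 1 + (m − 1)ρ, with m = 67/k dyads per CPN. The unadjusted type I error is 1 − Φ(1.645/√DE). Power of a valid test uses noncentrality 2.894/√DE and a t reference on 2(k − 1) df.

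Example, k = 3 (one per arm per site) and ρ = 0.02: m = 22.33; DE = 1 + 21.33 × 0.02 = 1.43; √DE = 1.19. Type I error is 8.4%. The noncentrality is 2.42 against a critical t of 2.13 on 4 df, so power is 64%.

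| CPNs per arm | ICC | DE | SE ratio | Unadjusted type I error | Power, normal reference | Power, t reference |
|---|---|---|---|---|---|---|
| 3 | 0.01 | 1.21 | 1.10 | 6.8% | 84% | 70% (4 df) |
| 3 | 0.02 | 1.43 | 1.19 | 8.4% | 78% | 64% (4 df) |
| 3 | 0.05 | 2.07 | 1.44 | 12.6% | 64% | 51% (4 df) |
| 6 | 0.01 | 1.10 | 1.05 | 5.9% | 87% | 82% (10 df) |
| 6 | 0.02 | 1.20 | 1.10 | 6.7% | 84% | 79% (10 df) |
| 6 | 0.05 | 1.51 | 1.23 | 9.0% | 76% | 71% (10 df) |

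Part of the loss in the last column is the price of few CPNs rather than of clustering: at an ICC of zero the same t reference gives 77% on 4 df and 85% on 10 df. With one CPN per arm at each site, a fixed site effect uses two further navigator-level df (6 − 1 − 1 − 2 = 2), so the 4 df figures are not a worst case.

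**Step 3: clustering in the DI arm only.** DE = 1 + (m − 1)ρ/2. For k = 3 and ICC 0.01/0.02/0.05 this is 1.11/1.21/1.53, with type I error 5.9/6.8/9.2%.

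**Step 4: unequal allocation.** With k = 3, ICC 0.05 and 2:1, DE is 1.94, type I error 11.9% and power (4 df) 49%. The pattern is unchanged.

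**Step 5: one CPN per arm.** At ICC 0.01, DE is 1.66 and type I error 10.1%. No df remain, so no model can separate the CPN from the arm.

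**Site.** Dyads are randomized individually and nothing suggests that sites are allocated to arms, so both arms are present at each site. Leaving out a factor crossed with arm leaves its variation in the residual and permits chance imbalance. It does not understate the standard error.

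**The case against.** *Dedication of CPNs is not stated for this trial.* The sentence reports what pilot studies taught, and no sentence says how CPNs are assigned here. This stands as a caution. If CPNs served both arms, the inflation would largely disappear. But the sentence directly follows this trial's blinding rule in the Intervention section and has little purpose there unless it describes current practice.

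*The size is assumed.* This also stands. Neither the number of CPNs nor an ICC is given. A common ICC in both arms may be generous, because the control arm's CPN role is lighter and part of the DI content is standardized audio and print. Step 3 shows the effect of that choice.

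*This is detail for a full protocol or analysis plan.* The article condenses a longer document, and its list of model terms need not be exhaustive. That would excuse silence, but the article is not silent. It names the model terms, names two sources of correlation for the additional analyses, and states a power figure that reproduces under independence.

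*Site.* A reader might infer that omitting site, with different catchments and one site starting in 2019, also makes the standard errors too small. The design does not support that, because site is crossed with arm. A reader might also take the normal-reference powers (84/78/64% with 3 CPNs per arm) as what a corrected analysis would achieve. With so few CPNs they are too optimistic, and the t-reference figures apply.

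**Conclusion.** The point holds for navigators. If CPNs are dedicated by arm, as the text implies, any positive CPN ICC makes the unadjusted standard error of the arm effect too small and the 89% too high. The direction is certain under that condition, but the size is not. For ICCs of 0.01 to 0.05, 3 CPNs per arm give an unadjusted type I error of 6.8% to 12.6% (5.9% to 9.2% if only DI is clustered) and power of about 70% to 51% on 4 df. Six per arm give 5.9% to 9.0% and 82% to 71% on 10 df. The two-arm figures rest on 1:1 allocation, one-sided alpha 0.05, equal caseloads and a common ICC. For site, the documents support only a loss of precision and a risk of chance imbalance.

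**What to change.** 1. State how CPNs are assigned to dyads, and how many there are per arm and per site.
2. Record the CPN's identity for each dyad, if this is not already done.
3. Add site as a fixed effect to the primary model.
4. Pre-specify an analysis with CPN as a random effect nested in arm and a small-sample correction, as a sensitivity analysis if CPNs are few. Report the ICC.
5. Describe the 89% as power under independence, and give a range over plausible ICCs for the actual number of CPNs and allocation ratio.
6. If there are only one or very few CPNs per arm, state as a limitation that navigator and arm effects cannot be separated.

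The cost is some added wording and at most one recorded variable. Confidence intervals may widen and the stated power will fall.
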